#### 16.4.2 Multiple comparisons

Considering the exploratory nature of the study endpoints no adjustments for multiplicity will be made. However, due to the large number of exploratory endpoints and many timepoints for evaluations, results for these endpoints will be interpreted with caution.

#### 16.4.3 Handling of missing data

Missing values will in general not be imputed in the analyses. Participants who withdraw from the study for any reason after receiving a study intervention but prior to the Day 8 assessment will be asked to complete an exit assessment of the primary study endpoint (change in MADRS total score from Baseline to Day 8 post-dose). It is anticipated that the temporal proximity of the primary endpoint to the study intervention, combined with efforts to obtain an exit assessment for participants who drop prior to the primary endpoint, will ensure that missing data (either missing at random or missing not at random) will be negligible.

Moreover, obtaining a MADRS total score at several occasions post dosing (Table 1) will provide additional data points prior to and after the Day 8 primary endpoint. Participants who receive a study intervention but miss the Day 8 post-dose assessment for any reason other than study discontinuation will be invited to continue in the study and all other

subsequent assessment points will be collected to allow the participant's data to be included in analyses of secondary endpoints, as well as the safety data.

#### **16.4.4 Interim analyses**

The primary analysis of this study will be conducted when all patients have completed the Day 42 assessment. The patients will continue in the study until Day 365 when the follow-up analysis will be done.

#### **16.4.5 Subgroup Analyses**

No subgroup analyses will be conducted.

#### **16.4.6 Safety Analyses**

All recorded AEs will be coded using MedDRA and presented by SOC and preferred term with number of subjects, percentages and number of events overall and by study period. The worst severity will be used for each event. TEAEs, solicited AEs, SAEs and AEs related to treatment will be summarized similarly. AEs leading to discontinuation from the study will be listed and tabulated.

All concomitant medications will be listed. Safety data collected for the period from Screening through the Baseline assessment and during the Preparation Phase will be presented separately from post-dose safety data (treatment emergent).

All solicited AEs observed in randomized participants who received psilocybin or niacin placebo will be reported.

## **17. SAFETY MANAGEMENT**

Below are the risks associated with participation in this study as well as the risk mitigation strategy associated with each risk. Safety measures will be applied, as described below, to minimize risks associated with participation in this study. This study proposes a combination of careful screening, preparation, supervision, and follow-up designed to minimize any risks.

Presented below are several domains that relate to adverse effects of psilocybin administration, which are further detailed in the IB. Following the section on psilocybin, the risks associated with the non-drug aspects of the study are described. Participation in this study may include risks that are currently unknown.

### **17.1 Risks Associated with Psilocybin**

#### **17.1.1 Physiological and Psychological Adverse Effects**

The clinical safety of psilocybin has been extensively studied, both as a single agent and as adjunctive treatment in adult populations. Psilocybin is administered orally, and has been studied in open-label, and double-blind, controlled trials. Dosing regimens have ranged from 0.014 mg/kg to 0.6 mg/kg, administered as either a single dose, or multiple doses weeks apart.

Adverse event data from previous clinical trials has been used to evaluate the physiological profile of psilocybin. The IB for psilocybin summarizes the adverse event data collected from controlled clinical trials utilizing psilocybin in conjunction with cognitive enhancement therapy across multiple subpopulations.

The most likely potential acute adverse effects of psilocybin has been shown to be anxiety, as well as panic, delusion, and cognitive impairments, particularly at higher doses (> 25 mg oral psilocybin) during the period of acute drug action. Such transient episodes of fear or anxiety respond well to verbal reassurance and have not required pharmacological intervention. In previous clinical experience, acute psychological events were resolved by the end of the dosing day.

Overall, the most commonly reported physiological adverse events associated with psilocybin are:

- cardiovascular changes (including increased blood pressure and heart rate)
- nausea
- headache

These adverse events were generally classified as mild to moderate and were found to be transient in nature. No psilocybin-related serious adverse events were reported.

### **17.1.2 Visual Perceptual Effects**

Some people who have used serotonergic hallucinogens, such as psilocybin, experience persistent, distressing alterations in mostly visual perception that last from weeks to years after use. This condition is now diagnosed as hallucinogen persistent perception disorder (HPPD).

To date, however, no cases of HPPD have occurred in volunteers given psilocybin in contemporary research studies. The risk of HPPD occurring after psilocybin administration can be reduced by screening participants for potential risk factors such as substance dependence and by excluding people reporting HPPD or other significant adverse events after prior use of hallucinogens.

Visual perceptual effects will be assessed as a solicited AE during Periods 3 and 4.

### **17.1.3 Drug Interactions**

See Appendix A for a list of prohibited medications. Additional information is provided in the IB.

### **17.1.4 Risk of Worsening MDD**

An exacerbation of depressive symptoms including increased suicidal ideation could occur prior to or during the study. Participants in the study will be foregoing established treatments for depression while they are enrolled in the study. This risk of having a depressive exacerbation may be greater for participants in the niacin placebo group, as they will undergo a longer period of time without receiving a known active treatment. Although placebo interventions often have significant therapeutic benefits in patients with MDD, participants who receive niacin placebo may be at increased risk for worsening of depressive symptoms or development of active suicidal ideation with plan during the course of the study.

Study clinicians at each site will assume the role of mental health provider when a participant enrolls in the study through the final primary outcome time-point at post-dose Day 42. Monitoring for suicidality will be ongoing. Study team members will inform a study clinician of any substantial worsening of depression or suicidality, or of any other concerns regarding a participant's health. Study clinicians will then assess the health and safety of this participant. If a study clinician decides that an antidepressant medication is warranted, or if the participant desires conventional treatment during or after the study, the study clinician will develop an appropriate treatment plan including referring the participant to an outpatient provider or to the clinician treating the participant prior to study entry.

## **17.2 Risks Associated with Collection of Potentially Sensitive Information**

Sensitive information may be revealed to study personnel during the screening process and/or during the course of the study. Identification of disease may occur during the screening process and may impact future insurability of the participant. In addition, some diagnoses can create stigmatization or self-stigmatization for the participant. Both the PI and participants may be at risk for a violation of privacy and/or loss of confidentiality. This risk will increase as the study progresses as ongoing health information will be collected.

Best practices will be followed at all stages of the study to ensure maximum protection in the collection, storage and usage of potentially sensitive information. All collected data will be stored on a secure electronic database coded by a study ID number and stored separately from any documents with personally identifiable information and/or a key that would link such information to study data. All research staff will complete GCP training to promote the proper conduct of scientific research in humans

## **17.3 Risks Associated with Recordings of Sessions**

To evaluate the Facilitators' adherence to the study manual, and the role of Facilitator's and participant's in-session behaviors for treatment outcome, the preparation session and all three integration sessions will be recorded using a digital voice recorder. The dosing session will be documented using a digital film camera. There is a risk that these recordings of sessions will make participants feel monitored, controlled and/or in any other way uncomfortable. However, recording of treatment sessions is a standard procedure in graduate and advanced therapist training, and as long as clients understand the purpose of the confidential recordings, they are often happy to consent. Clients who agree to being recorded are also generally happy to do so, and the recording instruments are quickly forgotten. In this study, upon requests from the participant to further examine the details and small nuances of the dosing day experience, (parts of) the filmed dose session will be used during the integration sessions.

Study participants will be informed of the recordings of sessions (i.e., why the sessions are being recorded and what they are used for) at the In-Person Screening visit, before signing the informed consent. The recordings will be kept securely in a locked cabinet at Mottagningen för hjärnstimulering. Collected data will then be stored on a secure electronic database coded by a study ID number; separately from any documents with personally identifiable information and the key for linking such information to study data.

## **17.4 Risks Associated with Psychiatric Questionnaires**

The study psychiatric assessments may uncover strong and potentially disturbing feelings about the participant's past or present emotional state. While it is expected the risk for SAEs resulting from psychiatric assessments is very low, the likelihood of these risks occurring will be minimized by procedures described below.

Care will be taken to avoid bringing about undue psychological distress during the psychiatric interviews. This will be accomplished by using trained central and on-site raters and by collecting the "minimum necessary" information required for study purposes. In the event that a participant becomes unduly distressed, a study clinician will be immediately contacted, and an appropriate clinical intervention plan will be developed.

## **17.5 Risks Associated with venepuncture and arterial cannulation**

The risks of drawing blood include discomfort, bruising, infection, bleeding and fainting. The amount of blood drawn during the study (approximately 250 mls, at three different occasions, 2-3 weeks apart) will not have any adverse physiological effects, nor will it lead to any long-term distress. Risks for blood borne pathogens from accidental needle stick and during sample processing exist. Not uncommonly, a bruise may form at the puncture site. Arterial cannulation will be performed in local anesthesia after Allen's test in order to verify palmar collateral circulation.

To reduce risk of infection and bleeding standard sterile procedures for drawing blood will be used by certified personnel with extensive phlebotomy experience. To reduce the risk of fainting all participants will be asked about tendency to faint prior to venipuncture and will be placed in a recumbent position if they answer in the affirmative.

## **17.6 Risks Associated with lumbar puncture**

Lumbar puncture (LP) for CSF collection will be performed at two occasions some 2-4 weeks apart (all together ca 10 mL of CSF) and after MR-imaging of the head, which will enable identifying signs of increased intracranial pressure. LP will be performed in the L4-L5 or adjacent lumbar intra columnar spaces, with the participant either lying down on the side, or sitting, with maximal kyphosis in the lumbar segment, and in local anaesthesia. Still there is a risk of post LP headache. The first line of treatment for post-LP headache is recumbence, hydration and analgesics as needed. However, if post-LP headache persists after a day of such treatment, administration of an epidural blood patch will be considered.

## **17.7 Risks Associated with Positron Emission Tomography (PET)**

A tracer dose of [C]UCB-J is to be administered iv at two occasions. This is associated with a risk of infection and/or thrombophlebitis at the place of intravenous administration. The exposure to radiation is theoretically associated with a risk of DNA-damage that, in the case of faulty DNA-reparation, may result in non-functional protein synthesis. This is considered a potential mechanism for development of dysplastic events.

## 17.8 Contacting Emergency Services

Generally, if at any time during the study, including during your dosing session, study staff feel a participant is in danger of hurting him/herself or someone else then the study physician, PI and/or Lead Facilitator will be contacted immediately for further evaluation and follow up. In certain circumstances 112 may be called or the participant may be taken to the emergency room, including the following:

- If at any time during the study physician, PI and/or Lead Facilitator feels your situation is an emergency that requires immediate attention they will call 112 or the participant will be taken to the emergency room.
- If the participant becomes violent or aggressive during the dosing session and he/she does not respond to medications or calming by your session Facilitators, then the study physician, PI and/or Lead Facilitator may call 112, or the participant may be escorted to the emergency room.
- If the participant insists on leaving the research site before the dosing session is complete (they must remain on site for a minimum of 7 hours) and the study physician, PI and/or Lead Facilitator feels he/she is a threat to him/herself or others then they will call 112.
- If the study participant insists on leaving the research site before the dosing session is complete and the study physician, PI and/or Lead Facilitator do not feel he/she a threat to him/herself or others then they will call the support person previously identified to take the participant home.

If the study physician, PI and/or Lead Facilitator feels the participant may have a serious, but not urgent, psychiatric condition then he/she will be referred to his/her previously identified mental health provider, if one was identified, or to mental health services in the community.

## 17.9 Abuse Liability

Like other psychoactive drugs, psilocybin is sometimes used in a manner that jeopardizes the safety or well-being of the individual or others (e.g., driving while impaired; a pattern of use that interferes with work, school, or relationships). Under such circumstances, psilocybin would be said to be *abused*. However, psychedelic medicines such as psilocybin are not typically considered drugs of *dependence* in that they do not engender compulsive drug seeking behavior, consistent with the observation that they are not reliably self-administered in nonhuman animals. Further, they are not associated with a known withdrawal syndrome. Therefore, there is little risk that exposing human volunteers to psilocybin will leave participants physically or psychologically dependent on the compounds. In previous and ongoing studies with psilocybin, exposing individuals with either no history of hallucinogen use or a history of minimal use (e.g., less than 10 times total and not within the last 5 years) in the context of a supervised and controlled research setting has not resulted in reported instances of subsequent illicit hallucinogen abuse. In the meta-analysis conducted by Studerus and colleagues, the large majority of participants in psilocybin studies (approximately 90%) reported “no change” in their psilocybin use following their laboratory sessions, as well as “no change” in their overall drug consumption habits (e.g., use of alcohol, nicotine, cannabis, MDMA). Those who did report changes often described decreased consumption (see Table 5 in Studerus et al., 2011). Specifically, in terms of psilocybin use, more participants reported using it *less* often after their laboratory sessions (5.6% of all participants) than more often (3.3% of all participants).

### 17.9.1 Abuse Monitoring

Based on current information, it does not appear that psilocybin demonstrates signals associated with known abuse liability patterns when administered in a therapeutic setting under continuous observation in a single-dose session, for which further evidence will be collected in this phase 2 study. Any abuse potential is further limited since the drug is not supplied to the participant to take home and is administered under careful clinical supervision in a restrictive setting. Participants will never have the study drug in their possession or have access to it outside the closely supervised clinical setting, which removes the possibility of drug diversion (e.g., missing medication, loss of drug) or unrecognized non-compliance with medication ingestion. While there is still a possibility of site drug diversion, this risk is mitigated through Drug Accountability process, documentation and monitoring.

The following measures will be employed to monitor the abuse liability of psilocybin:

- Cases of noncompliance, protocol violations, participants lost to follow-up, and any other reasons why participants dropped out of the study will be assessed for signals of abuse
- Qualitative urine drug test data will be collected at Screening, Baseline and all post-dose assessments. Any positive findings that cannot be attributed to pre-approved concomitant medications or diet will be reviewed by the site medical clinician for evaluation and management.
- Prior lifetime illicit and non-prescription drug use will be collected at Screening via the MINI interview and reassessed by self-report from Baseline to Randomization. Self-reported behaviors of alcohol and illicit and non-prescribed drug use will be collected via the AUDIT and DUDIT at web screening. Additionally, urine drug screens, as described above, will be used to identify drug use during the study period. Behaviors will be compared before and after intervention in exploratory analyses. These measures will be used to provide objective data to assess the impact of single-dose psilocybin on addictive behaviors, not just in relation to non-study psilocybin use but also in relation to other addictive substances/behaviors.
- Assessment of solicited AEs to identify drug and alcohol abuse/misuse as defined by the MINI, identification of substance and alcohol use disorders as defined by the MINI, and overdose with suicidal intent.

Evidence of any substance or alcohol use will be captured through the above measures and will not be reported as an AE. Should any substance or alcohol use be considered a SAE, it will be reported on a SAE form in addition to being captured through the assessments described above.

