### 5.4.1 Specific Safety Monitoring Objectives

Safety will be continually evaluated by study staff through monitoring and assessment of AEs, vital signs, concomitant medication use, physical exams, on-site rater administered measures, and integration with session Facilitators. The study will also assess abuse liability, including non-clinical, illicit use of psilocybin and other psychedelics and other illicit and non-prescribed drug use via the AUDIT and DUDIT, participant self-report, and urine drug testing per the Schedule of Assessments.

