### **5.6.3 Laboratory Assessments**

The following laboratory assessments will be performed at screening: Complete Blood Count with Differential (CBC w/ Diff), PK-INR, APTT, Na, K, creatinine, ALAT, ASAT, ALP, Ca, albumin, CDT, PEth, Thyroid Stimulating Hormone (TSH), high-sensitivity C-Reactive Protein (hs-CRP), HBV, HCV, HIV. Urine Drug Test and Pregnancy Testing will be done at screening, PET1 and PET2.

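### The promised before/after comparison of substance use has no post-dose self-report or interview, and the only urine panel named does not list psilocybin

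*Protocol*

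**What the plan says.** Section 5.4.1 (Specific Safety Monitoring Objectives) commits the study to assessing abuse liability, "including non-clinical, illicit use of psilocybin and other psychedelics and other illicit and non-prescribed drug use via the AUDIT and DUDIT", together with participant self-report and urine drug testing, at the times in the Schedule of Assessments.

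Section 17.9.1 (Abuse Monitoring) describes the measures and adds that "Behaviors will be compared before and after intervention in exploratory analyses". The stated purpose is objective data on the effect of a single dose, "not just in relation to non-study psilocybin use but also in relation to other addictive substances/behaviors".

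On timing, 17.9.1 says "Self-reported behaviors of alcohol and illicit and non-prescribed drug use will be collected via the AUDIT and DUDIT at web screening". Lifetime drug use is taken at screening by the MINI and "reassessed by self-report from Baseline to Randomization". The section also places urine drug tests at screening, baseline and every post-dose assessment. Section 5.6.3 (Laboratory Assessments) differs: "Urine Drug Test and Pregnancy Testing will be done at screening, PET1 and PET2".

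On reporting, 17.9.1 closes with "Evidence of any substance or alcohol use will be captured through the above measures and will not be reported as an AE", except where the use amounts to an SAE. Section 18.1.3 nevertheless lists drug and alcohol abuse or misuse, as defined by the MINI, among the solicited adverse events.

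**The concern.** A before/after comparison needs the same thing measured on both sides of the dose. Here the tools that ask people about their use are all placed before it, and the biological test that continues after it is not stated to cover the substance of most interest.

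The design puts all the information in the missing half. Section 7.1.2 excludes anyone reporting any previous psychedelic use, so the pre-dose value is none by construction. Section 9.3.1 requires a negative urine drug test on the morning of dosing, so urine can show only new positives. If no post-dose measure can register psychedelic use, a report of no signal would reflect what was collected and not what participants did. The trial would then be unable to answer a safety question it sets itself, and an analysis plan could not restore the data.

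**Working it through.** The plan gives no figure for this comparison. Its one design calculation, 15 per group for the Day 8 MADRS, is not involved. It reproduces: a two-sample t-test with standardized difference 11/10 = 1.1 has 82.8% power at 15 per group.

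**Step 1: each measure against the schedule.**

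| Measure | Before dosing | Scheduled after dosing | Source |
|---|---|---|---|
| AUDIT | Web screening | 0 | 17.9.1; Table 1 |
| DUDIT | Web screening | 0 | 17.9.1; Table 1 |
| MINI | Screening visit | 0 | 5.6.1; 17.9.1; Table 1 |
| Drug-use self-report | Baseline to randomization | 0 | 17.9.1 |
| Urine drug test | Screening, PET1/baseline, morning of dosing | 1 visit (PET2) or all visits | 5.6.3 and Table 1, or 17.9.1 |

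The Day 42 to 365 part of Table 1 has no row for AUDIT, DUDIT, MINI or urine toxicology.

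**Step 2: the urine contradiction.** The synopsis lists post-dose visits on Days 1, 8, 15, 42 and 365. Under 5.6.3 and Table 1, urine is tested at 1 of these 5. Under 17.9.1 it is tested at 5 of 5. Table 1 puts PET2 at Day 15 ± 7, so on the first reading the last test falls no later than Day 15 + 7 = 22. On the second it falls at Day 365.

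**Step 3: what the urine test can see.** The only panel named is in the exclusion criteria (synopsis and 7.1.2). It lists amphetamines, barbiturates, buprenorphine, benzodiazepines, cocaine, cannabis/THC, methamphetamine, MDMA, methadone, opiates and PCP. It does not list psilocin, LSD, mescaline, DMT or alcohol. Assuming the same panel is used after dosing, testing at every visit would still not show classic-psychedelic use.

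**Step 4: the adverse-event route.** Section 18.1.3 defines abuse or misuse by the MINI, which is not repeated. The synopsis limits solicited events to the period from randomization to Day 8 and does not name abuse or misuse. Section 17.9.1 says substance use is not reported as an AE because the measures above it capture it, and for psychedelics Steps 1 to 3 show no measure that does.

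**Step 5: what better data could show.** Section 17.9 cites 3.3% of participants in earlier psilocybin studies as using psilocybin more often afterwards. Taking that only as an illustrative rate for this psychedelic-naive sample:
- Chance of at least one user among n: 1 − (1 − 0.033)^n, which is 40% for n = 15 and 63% for n = 30.
- One-sided 95% upper bound on the rate if none of n is a user: 1 − 0.05^(1/n), which is 18% for n = 15 and 9.5% for n = 30.

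A working instrument would therefore give a descriptive count, not a precise rate.

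**The case against.** The strongest reply is that post-dose monitoring does exist. Urine tests are scheduled after dosing on any reading, and the named panel can show new use of MDMA, cannabis, amphetamines, cocaine or opiates. This stands. A reader might infer that nothing after dosing could show use of any substance, and the documents do not support that.

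A reader might also compute that (365 − 22)/365 = 343/365 = 94% of follow-up lies after the last urine test. That figure takes one side of a contradiction. Section 5.6.3 and the Table 1 urine row are not exhaustive: both omit the dosing-morning drug test that 9.3.1 requires. A spot test does not cover days in any case. What stands is that the passages disagree.

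The panel sits in an eligibility criterion and is introduced as a list of inclusions, so its use after dosing is an assumption. This too is fair, although no other panel is given.

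Nor is every reporting route closed. SAE reporting remains, and 18.1.5 names development of drug abuse as an important medical event. Section 17.9.1 reviews dropouts and protocol violations for abuse signals, and 18.5 monitors adverse events to the end of the study. These routes may catch serious or volunteered cases. They do not ask each participant about use and cannot supply a before/after comparison.

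Finally, abuse liability is not among the safety endpoints in 5.4.2 or the exploratory endpoints in 5.3, and thirty participants say little about rare use. That limits the weight of the point. It does not supply the missing data.

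**Conclusion.** The point holds in limited form. AUDIT, DUDIT, the MINI and drug-use self-report have no post-dose time point, so the self-report side of the promised comparison has a before and no after. Urine testing is the only scheduled post-dose measure of substance use. It is placed at 1 or 5 of the 5 post-dose visits depending on the section and, on the assumption that the eligibility panel is reused, it does not cover psilocin or other classic psychedelics. New use of several other drugs could be detected. Non-study psychedelic use, or a change in AUDIT or DUDIT, could not.

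A reader might go further and conclude that self-sourced psilocybin contaminates the Day 365 MADRS and the time to antidepressant treatment. The documents give no rate for such use in this trial, and Section 9.10 raises functional unblinding for Facilitators only. The follow-up phase also already allows antidepressants and outside psychotherapy. Such use would not be captured systematically, but harm to those endpoints is not shown.

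This is a secondary safety-monitoring matter. The Day 8 primary analysis and the sample size are unaffected.

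**What to change.** 1. Add AUDIT, DUDIT and one explicit question on non-study psilocybin or other psychedelic use since dosing to the Day 42 and Day 365 columns of Table 1, and say so in 17.9.1. Both are existing in-person visits. Table 1 allots 5 minutes to each scale, so the cost is 5 + 5 = 10 minutes per visit plus one question, as added participant burden. No new visit is needed.
2. If these data will not be collected, remove the before/after sentence and the stated purpose about non-study psilocybin use from 17.9.1, and the psychedelic-use part of 5.4.1.
3. Reconcile the urine-test time points in 17.9.1, 5.6.3 and Table 1, and state which panel is used after dosing. This is a wording change, unless the reconciled schedule adds tests.
4. Reconcile the 17.9.1 statement that substance use is not reported as an AE with the MINI-defined solicited event in 18.1.3 and with the synopsis list and window. This is wording only, unless the MINI is to be repeated.
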